# Smokers making a quit attempt using e-cigarettes with or without nicotine or prescription nicotine replacement therapy: Impact on cardiovascular function (ISME-NRT) - a study protocol

**DOI:** 10.1186/s12889-017-4206-y

**Published:** 2017-04-04

**Keywords:** E-cigarettes, Nicotine Replacement Therapy, Microcirculation, Macrocirculation, LDF, FMD

## Abstract

**Background:**

The estimated number of cigarette smokers in the world is 1.3 billion, expected to rise to 1.7 billion by 2025, with 10 million smokers living in the U.K. Smoking is the leading, preventable death-cause worldwide, being responsible for almost 650,000 deaths in the E.U. annually. A combination of pharmacological interventions, including nicotine replacement therapy, bupropion and varenicline, and behavioural support is the most effective approach to smoking cessation. However, even the best methods have high relapse rates of approximately 75% within 6 months. Electronic (or “e-“) cigarettes use battery power to disperse a solution that usually contains propylene glycol or glycerine, water, flavouring and nicotine. E-cigarettes have become the most popular smoking cessation aid in England, however, information on their effects on cardiovascular function is limited and contradictory. As e-cigarettes are not solely nicotine-based products, existing research exploring the effects of nicotine on the cardio-vasculature provides only limited information, while their extensive uptake urges the need of evidence to inform the general public, smokers and policy-makers.

**Methods:**

This is a pragmatic, 3-group, randomised, assessor-blinded, single-centre trial exploring the cardiovascular physiological effects of the use of e-cigarettes (nicotine-free and nicotine-inclusive, assessed separately) combined with behavioural support as a smoking cessation method in comparison to the combination of NRT and behavioural support. The primary outcome will be macro-vascular function, determined by a Flow Mediated Dilatation ultrasound assessment, 6 months following participants’ “quit date”.

**Discussion:**

Participants will be assessed at baseline, 3 days following their self-determined “quit date”, at intervention end (3 months) and 6 months following their “quite date”. Findings are expected to give an indication of the cardiovascular effects of e-cigarettes both in the short- and in the medium-term period, informing the general public, policy holders and researchers, helping to define the future role of e-cigarettes as a smoking cessation aid.

**Trial registration:**

Clinicaltrials.gov NCT03061253. Registered 17th February 2017.

## Background

The estimated number of cigarette smokers in the world is 1.3 billion, expected to rise to 1.7 billion by 2025, with 10 million smokers living in the U.K [1]. Smoking is the leading, preventable death-cause worldwide [2], being responsible for almost 650,000 deaths in the E.U. annually [3].

**Fig. 1 Fig1:**
[figure not shown]
Participant study schedule

Smoking cessation could reduce total cardiovascular disease (CVD) mortality by 36% [2]. This is because the vascular endothelium plays a major role in cardiovascular health and disease (e.g. systemic and pulmonary hypertension, coronary heart disease and stroke; [4], and cigarette smoking has been associated with endothelial dysfunction in otherwise healthy adults [5] – with its detrimental effects ranging from early functional endothelial alterations to late clinico-pathological manifestations of atherosclerotic plaques [2]. The negative effects upon cardiovascular function are not limited to smokers; passive smoking increases heart disease death-risk by almost 30% [6].

A combination of pharmacological interventions, including nicotine replacement therapy (NRT), bupropion and varenicline, and behavioural support is the most effective approach to smoking cessation [7, 8]. However, even the best methods have high relapse rates of approximately 75% within 6 months [7] and although they are offered as part of the UK National Health Service (NHS), these interventions have been reaching fewer smokers (down about 50% from 2010/11 to 2015/16; [9]).

Cigarette smoke contains more than 9000 chemicals; the vast majority of which are the products of tobacco combustion [10]. The most important ones in regards to CVD risk are: oxidizing chemicals, carbon monoxide, volatile organic compounds, particulates, heavy metals and nicotine [11]. Therefore, and taking into consideration that nicotine is highly addictive [11], it is important, where complete abstinence is not possible, to encourage substitution of cigarettes with “cleaner” nicotine-based products to reduce CVD risk and reverse some of the smoking-induced physiological damage [12].

Electronic (or “e-“) cigarettes or vaping devices uses battery power to disperse a solution that usually contains propylene glycol or glycerine, water, flavouring and nicotine [13]. They have become the most popular smoking cessation aid in England [14], while evidence suggests that they are efficacious as smoking cessation aids [15]. However, data on their effects on cardiovascular function is limited i.e. [16] and there is a lack of consensus within the smoking cessation community as to their potential impact: consequently, further research has been requested by the European Parliament [17], the British Medical Association [18], regulatory agencies, clinicians and researchers Lancet; [19], BMC Public Health; [20]. As e-cigarettes are not solely nicotine-based products, existing research exploring the effects of nicotine on the cardio-vasculature (e.g. coronary and peripheral vasoconstriction, intravascular inflammation and deregulation of cardiac autonomic function as well as inhibition of microcirculation; [21]) provides only limited information. Evidence is needed to inform the general public, smokers and policy-makers.

This study aims to assess effects on cardiovascular physiology in smokers making a quit attempt using e-cigarettes (either nicotine-free or nicotine-inclusive) in comparison with smokers making a quit attempt with prescription NRT.

The specific objectives of the study include:The comparison of the effects that nicotine-inclusive e-cigarettes (Group A), nicotine-free e-cigarettes (Group B) and NRT (Group C) have on cardiovascular physiology both acutely (e.g. within 3 days of “quit date”) and in the medium term (6 months following “quit date”), by measuring: a) endothelial-dependent, macro-vascular function and b) endothelial-dependent, micro-vascular function. The inclusion of Group B (nicotine-free e-cigarettes), will allow us to determine whether the e-cigarette vapour constituents have a distinguishable effect on cardio-vasculature against a nicotine-inclusive e-cigarette (Group A).Comparison of the effect of the different treatments on cardiovascular disease risk.An in-depth exploration of the participants’ study experience in a sub-sample of participants.Defining facilitators and barriers of smoking cessation in each of the 3 groups.Assessing the economic cost implications that the approaches have on the NHS and the study participants, by undertaking a Health Economics’ Cost Utility Analysis.

## Methods

### Design

A pragmatic, 3-group, randomised, assessor-blinded, single-centre trial exploring the cardiovascular physiological effects of the use of e-cigarettes (nicotine-free and nicotine-inclusive, assessed separately) combined with behavioural support as a smoking cessation method in comparison to the combination of NRT and behavioural support.

### Study setting

All assessments will be undertaken at the Centre for Sport and Exercise Science (CSES) of Sheffield Hallam University. Behaviour support will be primarily provided in Sheffield Hallam University premises in Collegiate Crescent or City campuses to cover the widest possible Sheffield population, with both locations being easily reached from all Sheffield areas. This setting was chosen to ensure appropriate data collection, to assess its acceptance by participants and monitor their physical and emotional wellbeing, as the university has extensive experience of delivering lifestyle interventions to clinical populations (e.g. cancer, heart failure, aortic aneurysm, chronic venous insufficiency and intermittent claudication). Group C will be referred to NHS smoking cessation clinics in Sheffield (*Yorkshire Smokefree Sheffield*), provided by South West Yorkshire Partnership NHS Foundation Trust.

### Eligibility

*Inclusion Criteria*
Age > 18 years of either sex,Smokers (at least 10 cigarettes/ day for the past year),Willing (by declaration) to attempt quit smoking by using the NHS services or e-cigarettes.

*Exclusion Criteria*
Inability to walk,Recent (within 6 months) cardiovascular disease event (e.g. stroke, myocardial infarction) or cardiac surgery,Insulin-controlled diabetes mellitus or with coexisting skin conditions, leg ulcers, vasculitis or deep venous occlusion (as these may affect their cardiovascular function),Pregnancy,Requiring major surgery during the course of the study),Contraindications /unsuitability for NRT,Current daily use of e-cigarettes,Currently undertaking a cessation attempt supported by a smoking cessation clinic,Unable to give informed consent.

*Withdrawal*s.

Participants will be considered as withdrawn from the trial if they request to leave the trial, if they are lost to follow-up, or if they die before completing the 12-month follow-up.

Participants will be considered as withdrawals from the allocated treatment if they no longer use the electronic cigarette, or if they no longer receive NRT-based, smoking cessation therapy. Withdrawals from the trial and from the allocated treatment will be included in the analysis by intention-to-treat. Standard care for participants who decide to withdraw from the study will not be affected.

### Recruitment and consent processes

Recruitment from the community in the wider Sheffield area will be via: i) low-cost newspaper and post-office advertisement, ii) posters in local pharmacies, libraries, mosques, churches, and clubs, iii) social media or search engine advertisement (Facebook, Google ads) iv) notices in newsletters or participation in outreach events of community organisations (such as Sheffield U3A and AGE UK), iv) a study website and v) out-reach events in local ethnic community centres or places of worship.

Potential participants will be provided with a study information pack by post, via e-mail or in person, containing an invitation letter (including also the contact details of a research team member), a study information sheet and a stamped, addressed envelope with a tear-off slip to declare their interest (or not) to take part in the study. Following receipt of an “expression of interest” slip/phone call/e-mail, a researcher will contact the patient by telephone and their first visit will be arranged. Smokers who express interest and do not respond within 14 days of the research team posting them an information sheet, will be contacted one more time. During Visit 1 written informed consent will be obtained and eligibility confirmed. The participant schedule for the study is shown in the Fig. 1.

### Resource use diary, randomisation and blinding

After completion of baseline assessments (Visit 1), participants will receive the “resource use” diary together with instructions as of how to complete it. The diary will elicit information on utilisation of NHS and private health care services related to smoking cessation or smoking-related diseases and condition. It is proposed to collects three items of information (1) number of visits, (2) travel time and cost and (3) cost to the patient for the following uses: (a) GP, (b) nurse at smoking cessation clinics, (c) Nurse at smoking cessation clinics (d) Psychologist/Counsellor. Similarly number of times and the costs to the patient for undertaking (1) diagnostic tests (X-rays, Blood test and any other tests) and (2) medications (pain killers, sleeping pills, antibiotics, nicotine patches, any other) related to smoking cessation. Further, number of days of hospitalisation related to smoking related diseases will also be collected.

They be randomised remotely (to ensure allocation concealment) into Groups A (using the nicotine-inclusive e-cigarette), B (using the nicotine-free e-cigarette) and C (being referred to NHS clinic), using a computer programme (nQuery Advisor 6.0, Statistical Solutions, Ireland) to generate stratified block-randomization (by gender and “packet-years” (e.g. number of packs (20 cigarettes per pack)/day x number of years smoked), by an independent statistician. Each participant will be allocated a unique trial number that will remain with him/her throughout the study.

Outcome assessors will be blinded to group allocation and participants will be reminded regularly not to share their group allocation with this person. Statistician and health economist will be blinded to group allocation during the analysis process.

### Sample size

For the purposes of sample size estimation the primary outcome will be macro-vascular function, at 6-months post-“quit date” follow-up, as measured by % Flow-mediated dilatation FMD; [22]. For our calculations we used commercial software (G*Power 3.1.7, HHU of Düsseldorf).

Based on the primary outcome and using data comparing the short-term effects of e-cigarettes on macro-vascular function (measured by %FMD) in smokers and non-smokers (S.D. in the smokers’ group prior to e-cigarettes’ use = 3.23%, expected brachial FMD% difference between NRT group and e-cigarette users = 1.89%; 16). Using G*Power 3.1.7 (HHU of Düsseldorf) we calculated that we will need 66 participants in each group to detect a difference in macro-vascular function at 6 months (significance level = 0.05; power = 80%). Accounting for an estimated 25–30% dropout rate in-line with other e-cigarette-based RCTs [15], we aim to recruit 86 participants in each group (258 in total).

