### Data analysis

SPSS 21.0 will be used to enter quantitative data and cleaning the data and to carry out missing values imputation and statistical analysis. Data will be reported and presented according to the revised CONSORT statement [33].

Analyses will be performed on an intention-to-treat basis. Double data entry will be implemented to to promote data quality. Where applicable, tests will be two-tailed with statistical significance being set at *p* ≤ 0.05. Baseline demographic (i.e. age, gender, HSI), physical measurements (e.g. weight, height, BMI), carbon monoxide and nicotine dependence levels, as well as Q-Risk, SF-IPAQ and EQ5D-L will be assessed for comparability between groups.

An Analysis of Variance (ANOVA) will be used to compare mean macro- and micro-vascular function between groups. A 95% confidence interval (CI) for the mean difference in these parameters between the three groups will also be calculated. In the event of differences between groups with respect to baseline measurements, multiple regression will be used to adjust the treatment effect for these variables, with the stratification covariates being included in the analysis. The ordinary least squares adjusted regression coefficient estimate for the e-cigarette groups’ parameter, along with its 95% CI, will then be reported. Secondary outcomes at 6-months will be analysed similarly. For repeated assessments at baseline, and at all follow-up sessions a summary measure (e.g. “Area under the Curve”) will be calculated for each participant.

Finally, a further subgroup analysis of those who ceased smoking completely will be undertaken and results will be compared amongst the three groups.

For qualitative data analysis, audio recording of the interviews will be made, transcribed verbatim, and the five stages of framework analysis of familiarisation, identifying a thematic framework, indexing, charting, and mapping will be followed [34, 35].

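### The 1.89-point FMD difference comes from short-term data and is not justified for the 6-month intention-to-treat contrast, so the 80% power statement is unsupported

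*Protocol article*

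**What the plan says.** The Sample size section derives its inputs "using data comparing the short-term effects of e-cigarettes on macro-vascular function". From there it takes an SD of 3.23 for smokers before e-cigarette use and an "expected brachial FMD% difference between NRT group and e-cigarette users = 1.89" percentage points. With "significance level = 0.05; power = 80"%, it concludes that "we will need 66 participants in each group to detect a difference in macro-vascular function at 6 months". It then raises 66 to 86 per group (258 in total) for an expected 25–30% dropout.

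The analysis is of a different quantity. Under Withdrawals in the Eligibility section, a participant who no longer uses the e-cigarette or no longer receives NRT-based therapy counts as withdrawn from treatment, and "Withdrawals from the trial and from the allocated treatment will be included in the analysis by intention-to-treat". The Data analysis section confirms ITT and makes complete quitters a further subgroup analysis. Behavioural support runs for 3 months (Intervention), which the Outcome measures section treats as the end of the interventions. The primary outcome is read at 6 months. The Background states that "even the best methods have high relapse rates of approximately 75% within 6 months".

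**The concern.** A difference taken from short-term e-cigarette data is used as the mean difference between randomised groups at 6 months. By then supported treatment has been over for 3 months, and some participants in every arm will have stopped the product, returned to smoking, or both. Dropout inflation covers missing measurements. It does not cover participants who attend the 6-month visit and contribute an FMD value that no longer reflects the allocated product. The sample-size text contains no allowance for relapse, for stopping the product, or for a short-term effect that fades.

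What is at stake is how the primary result is read. A non-significant difference set against a stated 80% power invites the conclusion that the products differ little in vascular effect. It could equally arise because the 6-month ITT difference was smaller than the one used for planning.

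**Working it through.** **Inputs.** Difference 1.89 points, SD 3.23, alpha 0.05, power 80%, 66 per group (Sample size). Two-sided testing (Data analysis: "tests will be two-tailed with statistical significance being set at" 0.05). Recruited 86 per group with 25–30% dropout (Sample size). At 30% dropout, 86 × 0.70 = 60.2, so about 60 remain. At 25%, 86 × 0.75 = 64.5. The calculations use 66 and 60 as the two ends of the range.

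**1. The plan's own figure.** Standardised difference = 1.89 / 3.23 = 0.585. By the normal approximation, n per group = 2 × (1.960 + 0.842)² / 0.585² ≈ 45.9, so 46; the exact t-test gives 47. A three-group ANOVA needs 44 if both e-cigarette arms differ from NRT by 1.89, or 58 if the three means are evenly spaced over 1.89. None of these gives 66, and the section offers no reason for the excess.

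**2. Power for the full 1.89.** The noncentrality is (δ / SD) × √(n / 2).
- n = 66: 0.585 × √33 = 3.36, power 92%.
- n = 60: 0.585 × √30 = 3.20, power 89%.

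**3. Difference detectable at 80% power.** Solving the exact t-test for δ:
- n = 66: 1.587 points, and 1.587 / 1.89 = 84% of the design difference.
- n = 60: 1.666 points, and 1.666 / 1.89 = 88%.

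Power therefore stays at or above 80% until about 16% (66 per group) or 12% (60 per group) of the difference is lost.

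**4. Scenarios.** The share of 1.89 retained in the 6-month ITT contrast is an assumption; the protocol gives no value for it.

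| Share retained (assumed) | ITT difference | Power, 66 per group | Power, 60 per group |
|---|---|---|---|
| 100% | 1.89 | 92% | 89% |
| 75% | 1.42 | 71% | 66% |
| 50% | 0.945 | 39% | 36% |
| 25% | 0.47 | 13% | 13% |

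A three-group ANOVA at 66 per group, with both e-cigarette arms differing equally from NRT, gives 94%, 74%, 39% and 13%. With evenly spaced means it gives 86%, 60%, 30% and 11%. The pattern does not depend on the choice of test.

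**5. What the relapse figure would imply.** If 75% relapse and relapsers keep half the difference, the retained share is 0.25 + 0.75 × 0.5 = 0.625. The difference is then 1.18 points, with power 55% at 66 and 51% at 60. To hold 80% power at 66, relapsers would have to keep (0.84 − 0.25) / 0.75 = 79% of it.

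**The case against.** A reader might infer that the stated 80% power is not delivered, or that on the protocol's own figures the trial has 13% power. The documents support neither, for these reasons.

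- There is slack. At 66 per group, power for 1.89 is 92%, so some dilution can be absorbed.
- The 75% is a background rate for the best existing cessation methods. It is not a planning assumption for these three arms, and no rate is given for e-cigarettes.
- The 25% row is severe. It assumes that relapsers keep none of the difference, and it applies the relapse rate to participants left after dropout. If the dropouts were mostly relapsers, 25% of 86 is 21.5 people, or 33% of 66 and 36% of 60, with power about 19–21%.
- Quit rates may differ between arms. That alone would shift mean FMD and could enlarge or shrink the ITT difference.
- The phrase about e-cigarette users may simply mean Groups A and B, and the derivation of 1.89 from the cited source cannot be checked here.

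All of this stands, and it limits the claim. It does not remove the mismatch between short-term data and a 6-month ITT endpoint, which does not depend on how that phrase is read. Nor can the slack be taken as a planned allowance for relapse: the section does not mention one, and the excess over 47 is unexplained. It is also fair that no equivalence claim is planned and that smoking status is biochemically validated. Those features help interpretation but do not justify the power figure.

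**Conclusion.** The point holds in a limited form. The design difference is not justified for the contrast the trial will test, so the 80% power statement is unsupported; it has not been shown to be false. Power is adequate if the 6-month ITT difference is at least about 1.59 points with 66 evaluable per group, or 1.67 with 60, and falls quickly below that. These figures assume that SD 3.23 applies at 6 months, a two-sided 0.05 test and no multiplicity adjustment. With a Bonferroni correction over three pairwise tests (an assumption), power for the full 1.89 at 66 would be 82% and almost no slack would remain. The size of any dilution is unknown. Separately, 66 does not follow from the stated inputs.

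**What to change.** Keep 258 participants and the ITT analysis. In the Sample size section:

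1. State that 1.89 points comes from short-term data and is not an estimate of the 6-month ITT difference.
2. Replace the 80% power statement with the ITT difference detectable at 80% power: about 1.6 to 1.7 points for 66 down to 60 evaluable per group.
3. Add a short table of power by share of the difference retained, such as the one above, labelled as assumptions. Note that unequal quit rates between arms could move the difference either way.
4. Correct the stated size: 1.89 and SD 3.23 need about 47 per group for 80% power. If 66 came from other inputs, state them.

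The cost is a rewording of one section. The stated power becomes less favourable; no participants or procedures are added.

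### The 66 participants per group do not follow from the printed SD, difference, alpha and power, which give 47 by t-test; the discrepancy is conservative and its cause cannot be told from the article

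*Protocol article*

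**What the plan says.** The Sample size section of the protocol article prints these inputs for the primary outcome, %FMD at 6 months:

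- the SD: "S.D. in the smokers’ group prior to e-cigarettes’ use = 3.23"%;
- the difference: "expected brachial FMD% difference between NRT group and e-cigarette users = 1.89"%;
- the error rates: "significance level = 0.05; power = 80"%.

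From these, using G*Power 3.1.7, it reports: "we calculated that we will need 66 participants in each group to detect a difference in macro-vascular function at 6 months". It then allows for dropout ("Accounting for an estimated 25–30% dropout rate") and sets the target: "we aim to recruit 86 participants in each group (258 in total").

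The section names no test, no alpha per comparison and no second SD. The Data analysis section supplies the sidedness ("tests will be two-tailed with statistical significance being set at" p ≤ 0.05) and the test: "An Analysis of Variance (ANOVA) will be used to compare mean macro- and micro-vascular function between groups". It states no multiplicity adjustment and no rank-based test.

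**The concern.** The article prints everything that a simple two-group calculation needs, together with the answer, and the two disagree by 19 participants per group (66 against 47, or 40% more). That is too large for rounding or for the choice between a normal and a t approximation.

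This is the justification for the size of the trial on its primary outcome. As printed, a reader cannot tell which comparison, test, SD or alpha the trial was sized for. The answer matters because there are three groups. On the printed SD and difference, 60 to 64 evaluable per group have power to spare for one comparison at alpha 0.05, but only about the 80% target if alpha were split over three pairwise comparisons.

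**Working it through.** **Inputs.** From Sample size: SD 3.23, difference 1.89, alpha 0.05, power 0.80, stated result 66 per group, 86 recruited, dropout 25–30%. From Data analysis: two-sided tests, three-group ANOVA. The SD is taken as common to all groups, since only one is printed.

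**Standardised difference.** d = 1.89 / 3.23 = 0.585.

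**Attempt to reproduce 66: two-sample comparison.**
- Normal approximation: n = 2(1.960 + 0.842)² / d² = 2 × 2.802² / 0.585² = 45.8, so 46 per group.
- Exact noncentral t: power is 79.3% at 46 and 80.1% at 47, so 47 per group.
- One-sided t: 37 per group.

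**Attempt to reproduce 66: three-group ANOVA (noncentral F, 2 numerator df).**
- One group differs from the other two by 1.89: f = d√2 / 3 = 0.276, giving 44 per group.
- Means equally spaced over 1.89: f = d / √6 = 0.239, giving 58 per group.
- A generic f of 0.25: 53 per group.

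**Rank test at the stated alpha and power.** A Wilcoxon-Mann-Whitney test needs 50 per group (normal-data efficiency) or 55 (minimum efficiency).

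None of these reaches 66.

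**What 66 per group would deliver on the printed inputs.** The two-sided t-test at alpha 0.05 has 91.6% power. The difference detectable with 80% power is 1.59.

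**Routes that reach 66 or come near it.** Each needs something that the article does not print.

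| Departure from the printed inputs | n per group |
|---|---|
| Common SD of about 3.85 (3.82 to 3.84 give exactly 66), t-test | 66 |
| Dropout already included: 46 / (1 − 0.30) = 65.7 | 66 |
| 90% power | 63 (t), 66 (rank test, normal-data efficiency) |
| Alpha 0.05/3 | 63 (t), 66 (rank test, normal-data efficiency) |
| Alpha 0.05/2 | 57 (t), 66 (rank test, minimum efficiency) |

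**What the recruited number delivers.** Evaluable per group: 86 × 0.70 = 60.2 and 86 × 0.75 = 64.5. Pairwise t-test on SD 3.23 and difference 1.89:

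| Evaluable per group | Power, alpha 0.05 | Power, alpha 0.05/3 |
|---|---|---|
| 60 | 88.9% | 78.0% |
| 64 | 90.7% | 81.0% |

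**If 47 is the intended figure.** Dropout inflation gives 47 / 0.75 = 62.7, so 63, and 47 / 0.70 = 67.1, so 68 per group. A target of 86 is then above what this calculation requires.

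**The case against.** The best defence is that the article never says that 3.23 is the SD in every group. It describes the SD of smokers before e-cigarette use in a cited study. If a pooled SD of about 3.85 was used, then 66 follows from an ordinary t-test with the stated alpha and power. A condensed article may also leave the G*Power test option to the full protocol. This stands as far as it goes. It removes any ground for saying that 66 was miscalculated, but it does not rescue the text, which presents 3.23 as the SD behind the figure and prints no other.

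A reader might go further and infer that the stated alpha, power or test cannot be the one used, or that the trial was sized with a multiplicity-adjusted alpha that was then dropped from the analysis. The document supports neither. The larger SD keeps the stated alpha and power and an ordinary t-test. Dropout counted early is another route. Several unrelated combinations land on exactly 66, so a match does not identify the method. Nothing in the article mentions an adjusted alpha or a rank test.

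Nor does the discrepancy show an underpowered trial. It runs the other way: 66 exceeds what the printed inputs require, and no planned analysis depends on that number.

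**Conclusion.** The point holds as a failure to reproduce. On the printed SD, difference, alpha and power, the requirement is 47 per group by two-sided t-test, or 44 to 58 by three-group ANOVA over the two patterns of means examined. The stated 66 corresponds to about 92% power instead of 80%, or to a detectable difference of about 1.59 instead of 1.89. This rests on one common SD of 3.23 and on two-sided testing, as the Data analysis section specifies.

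Confidence is high that 66 does not follow from what is printed. The cause is unknown. Because the discrepancy is conservative, leaving about 89 to 91% power for one unadjusted pairwise comparison, it should be fixed but does not threaten the trial's validity.

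**What to change.** Retrieve the G*Power record. Restate in the Sample size section the comparison, test, SD or SDs, alpha per comparison, power and dropout step that were actually used, so that together they reproduce 66. Make the alpha agree with the one in the Data analysis section. The inputs should come from that record and not be chosen afterwards because they happen to return 66.

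If the printed inputs are the intended ones, correct 66 to 47, keep 86 per group (258 in total) as the target, and justify it by the power that 60 to 64 evaluable per group give: about 89 to 91% for one unadjusted pairwise comparison.

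Either way the cost is protocol wording only, and recruitment is unchanged. In the second case 86 must be given its own justification, because it can no longer be presented as 47 plus a dropout allowance.

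### Recruiting 86 per group does not leave the 66 per group the plan says it needs at its own 25–30% dropout; it leaves about 60 to 64

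*Protocol article*

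**What the plan says.** All the figures stand in the Sample size section of the protocol article. The primary outcome there is % FMD at 6 months after the quit date.

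- Evaluable requirement: "we will need 66 participants in each group".
- Design inputs: "significance level = 0.05; power = 80" (per cent), "expected brachial FMD% difference between NRT group and e-cigarette users = 1.89" (per cent) and "S.D. in the smokers’ group prior to e-cigarettes’ use = 3.23" (per cent).
- Allowance for loss and recruitment target: "Accounting for an estimated 25–30% dropout rate in-line with other e-cigarette-based RCTs [15], we aim to recruit 86 participants in each group", which the section gives as 258 in total.

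The section prints no inflation formula and gives no reason for 86 other than dropout. The Data analysis section adds that "tests will be two-tailed", that analysis is by intention to treat, and that missing values will be imputed. It does not link any of this to the recruitment target.

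**The concern.** A dropout rate is a share of the people recruited, so the number left is the recruited number times (1 − dropout). If 66 must remain and 25–30% are lost, the recruited number has to be 66 divided by (1 − dropout). The printed 86 is below that quotient at every point of the stated range.

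The primary outcome needs an ultrasound measurement at the 6-month visit, so dropout acts directly on the evaluable number. The article tells its readers that a 25–30% loss is already covered. As written, it is not, and the stated 80% power is attached to a number that the recruitment target is not expected to deliver.

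**Working it through.** **Inputs (all from Sample size, except sidedness, which is from Data analysis).** Required evaluable n = 66 per group; dropout d = 0.25 to 0.30; recruited = 86 per group, 258 in total; difference 1.89; SD 3.23; alpha 0.05, two-sided; power 80%.

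**1. Reproducing 86.**
- n × (1 + d): 66 × 1.25 = 82.5; 66 × 1.30 = 85.8, which rounds up to 86.
- n / (1 − d): 66 / 0.75 = 88; 66 / 0.70 = 94.3, rounded up to 95.

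The printed 86 is consistent with adding 30% to 66. Division gives 88 to 95 over the stated range and never 86. As no formula is printed, the route is an inference; the mismatch does not depend on it.

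**2. What 86 leaves.**

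| Dropout | Evaluable per group, 86 × (1 − d) | Short of 66 by | Recruitment needed for 66 | Total, three groups |
|---|---|---|---|---|
| 25% | 64.5 | 1.5 | 88 | 264 |
| 30% | 60.2 | 5.8 | 95 | 285 |

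Over all three groups, 258 leaves 193.5 at 25% and 180.6 at 30%, against 3 × 66 = 198.

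**3. Largest dropout that 86 covers.** 1 − 66/86 = 20/86 = 23.3%.

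**4. Effect on power, if 66 is taken as giving exactly 80%.** By the normal approximation, power at n per group is Φ[(1.960 + 0.842) × √(n/66) − 1.960].
- n = 64: 2.802 × 0.985 − 1.960 = 0.80, power about 79%.
- n = 60: 2.802 × 0.953 − 1.960 = 0.71, power about 76%.

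This reading implies a standardised difference of about 0.49, which the document does not print.

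**5. Effect on power, from the printed difference and SD.** The standardised difference is 1.89 / 3.23 = 0.585. For one two-sided pairwise comparison at 0.05 and 80% power, n = 2 × (1.960 + 0.842)² / 0.585² ≈ 46 per group by the normal approximation, and 47 by the exact t calculation. Exact power at 60 and 64 per group:

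| Test | n per group for 80% | Power at 60 | Power at 64 |
|---|---|---|---|
| One pairwise t-test, alpha 0.05 | 47 | 88.9% | 90.7% |
| Pairwise t-test, alpha 0.05/3 (an assumption; the plan does not state it) | 63 | 78.0% | 81.0% |
| Three-group ANOVA, one mean differs by 1.89, other two equal | 44 | 91.8% | 93.4% |
| Three-group ANOVA, outer means differ by 1.89, third midway | 58 | 81.9% | 84.5% |

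None of these gives 66, so the requirement itself is not reproduced from the inputs printed beside it.

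**The case against.** The strongest objection concerns the consequence. A reader might infer that the trial will fall below 80% power under its own assumptions. The document does not support that. The 79% and 76% in step 4 hold only if 66 is exactly the 80% point, and that needs an effect size printed nowhere. On the printed difference and SD, 60–64 per group gives about 89–91% for a single pairwise test, and more than 80% for the three-group ANOVA under either pattern of means shown. Power touches the 80% line only under a three-comparison correction that the plan does not mention. This part of the objection stands and limits the point to a mismatch between stated figures.

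It is also fair to say that the gap at 25% dropout is close to rounding (86 against 88). That stands for the lower end, but not at 30%, where the gap is 9 per group, or 27 in total. It stands too that multiplication by 1.30 is only the likeliest explanation of 86.

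Two other defences fail. Intention-to-treat analysis and imputation keep withdrawn participants in the analysis, but they do not restore the information lost when the 6-month FMD is not measured, and the plan does not offer them as a reason for 86. Nor is this a detail left to a fuller document: requirement, dropout and target are all printed here, and they conflict.

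**Conclusion.** The point holds as an inconsistency between printed figures. With 86 recruited per group and 25–30% dropout, about 60 to 64 per group are expected to be evaluable, roughly 2 to 6 fewer than the 66 declared necessary (2–9% of 66). This assumes that the dropout rate is a share of those recruited, that it is similar in the three groups, and that those who drop out have no 6-month FMD.

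The loss of power is at most about 1 to 4 percentage points if 66 is accepted as the 80% point, and power below 80% is not shown on the printed difference and SD. That 66 does not follow from those inputs is a separate matter, but it decides which power can be quoted for 60–64. Severity: should-fix. A figure the trial relies on is wrong as written, but the correction changes neither the design nor the analysis.

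**What to change.** Keep 86 per group and replace the dropout sentence with: *With 86 randomised per group and 25–30% dropout, 60–64 per group are expected to be evaluable.*

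Follow it with the power at 60 and at 64 per group, naming the test, effect size, SD and alpha that produced 66. This has to come after 66 has been reconciled with the printed 1.89 and 3.23. Otherwise the new sentence would either quote about 89–91% beside a claim that 66 are needed for 80%, or quote 76–79% on an effect size that the reader cannot find.

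If the sponsor prefers to guarantee 66 evaluable, the targets are 88 per group (264 in total) at 25% dropout and 95 per group (285 in total) at 30%, that is 6 or 27 more participants than 258.

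The preferred correction costs one or two sentences and a short recalculation. It needs no extra enrolment. The stated evaluable number becomes slightly less favourable; the stated power may move either way, depending on the basis that is named.
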